#### Letrozole

Women in the letrozole group will receive letrozole without acupuncture. One pill of letrozole (2.5 mg) (Femara; Novartis Pharmaceuticals, Basel, Switzerland) will be started between days 3 and 7 of the spontaneous menstrual cycle or between days 3 and 7 after a withdrawal bleeding following progestin. After the initial dose, one pill will be taken for the next 4 consecutive days (five pills total). If there is a response with ovulation (i.e., the serum progesterone level on day 21 or day 28 of the cycle is > 3 ng/ml), this dose will be maintained and will be given between days 3 and 7 of the next cycle. In those with no ovulatory response, day 28 of the cycle will be regarded as day 1 of the next cycle. For the new cycle, letrozole will be started on day 1, and the letrozole dose will be increased to 5 mg (two pills) per day for 5 consecutive days. If there is still no response, the dose will be increased to 7.5 mg (three pills) per day for 5 days in the next cycle. The maximum daily dose of letrozole will be 7.5 mg daily for 5 consecutive days.

#### Placebo letrozole

Women in this group will receive placebo letrozole with no acupuncture. Placebo letrozole will have the same appearance as letrozole (Dongyangguang Pharmaceutical Co., Ltd., Guangdong, China) and will be given according to the same schedule as letrozole.

### Randomization and patient allocation

The web-based Research Management database system (ResMan; www.medresman.org) will be used to allocate patients in a 1:1:1:1 ratio. The data coordinating center (DCC) statisticians will generate and validate the randomization scheme for the study before it is implemented in the ResMan database system. When a participant is enrolled, an investigator at the participating site will take out a sealed envelope and enter the identification number into the ResMan database system and will log in to a password-protected secured website designed by the DCC to determine the group allocation.

### Blinding

The acupuncture groups will be known only to the acupuncturists and the ResMan data manager. The letrozole and the placebo letrozole pills with the same appearance will be organized in a kit consisting of one cycle of pills for each participant, and one participant will at most take 45 pills over a total of 4 cycles. The sealed envelope with four cycles’ worth of pills will be labeled with an identification number mapped to the letrozole or placebo letrozole allocations, which will be known only to the ResMan staff. Participants and investigators will be blinded to the letrozole or placebo letrozole allocation. All outcome assessors and the statisticians performing the data analysis will be blinded to group allocation. Except for emergencies, unblinding of individual participants will not take place until all pregnant participants giving birth and the outcomes of the births have been reported to the DCC. In the event that emergency unblinding is needed, only the site principal investigators (PIs) will be able to unblind the participant to treatment by contacting the director of the DCC. The site PIs and DCC staff will receive notification from the central randomization service when emergency unblinding has occurred.

### Study-specific visits and procedures

Women will attend up to five different clinic visits, including the screening visit, the baseline visit, the treatment visits, the pregnancy visit, and the end-of-treatment visit (Fig. 2, Table 3). Adverse events (AEs) and concomitant medications will be recorded at every visit. Face-to-face adherence reminders will be given at each study visit.

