
### Intervention

All participants will be informed of the benefits of regular physical exercise and will be instructed to have regular intercourse every 2 to 3 days. Women in both the personalized and fixed acupuncture groups will receive acupuncture treatment three times per week with a maximum of 48 treatment sessions over 16 weeks. Acupuncture treatment will be started between days 3 and 7 of the spontaneous menstrual cycle or between days 3 and 7 after withdrawal bleeding following progestin. They will be contacted by phone if they miss the scheduled appointment. If they miss appointments during treatment, missed appointments will be clearly documented in the record for later analysis. They will be treated for up to 16 weeks. If they become pregnant, the treatment they are receiving will be stopped. For the personalized and fixed acupuncture groups, credibility and expectancy questionnaires will be completed at the third acupuncture treatment and at the last acupuncture treatment.

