**Fig. 2 Fig2:**
[figure not shown]
Study flowchart

**Table 3 Tab3:** Overview of the study visits

	Screening visit	Baseline visit	Treatment visits (16 weeks)				End-of-treatment visit	Pregnancy visit
			Personalized acupuncture	Fixed acupuncture	Letrozole	Placebo letrozole		
Sign consent	×							
History	×						×	
Urine pregnancy test	×	×	×	×	×	×		
Physical examination	×						×	
Transvaginal ultrasound	×							×
Semen analysis	×							
Tubal patency test	×							
HPV or TCT	×							
Preconception counseling	×							
Fasting blood for laboratory tests	×						×	
Blood sample collection		×					×	
Serum progesterone assay	×		×	×	×	×		×
Serum HCG assay	×	×	×	×	×	×		×
Questionnaires		×					×	
Acupuncture treatment (three times weekly)			×	×				
Assess adverse events and concomitant medications			×	×	×	×	×	×
Pregnancy and neonatal records								×

Physical examination: weight, height, waist circumference, hip circumference, Ferriman-Gallwey/acne

Fasting blood for laboratory test: follicle-stimulating hormone, luteinizing hormone, sex hormone–binding globulin, total testosterone, free testosterone, estradiol, prolactin, fasting blood glucose, fasting insulin, C-peptide, glycated hemoglobin, cholesterol, triglycerides, high-density lipoprotein cholesterol, low-density lipoprotein cholesterol, complete blood count, thyroid profile, renal profile, and liver profile

Transvaginal ultrasound: endometrial thickness, ovarian volume, antral follicle count, and size of ovarian cysts or developing follicles

Preconception counseling: TORCH (toxoplasmosis, rubella, cytomegalovirus, and herpesvirus) and human immunodeficiency virus screening

Blood sample collection: serum for the central core laboratory

*Abbreviations: HCG* Human chorionic gonadotropin, *HPV* Human papillomavirus, *TCT* ThinPrep cytologic test

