### Treatment visits

The women will be instructed to engage in intercourse once every 2 or 3 days. A serum progesterone measurement will be taken in the local laboratory on day 21 of the menstruation cycle. An elevated progesterone level > 3 ng/ml will be considered to indicate evidence of ovulation. If there is no ovulation, the serum progesterone level will be checked every week until ovulation. If ovulation occurs, a serum pregnancy test will be performed 1 week later. For the duration of the treatment, urine LH or human chorionic gonadotropin (HCG) levels can be measured, depending on the judgment of the PI, in order to obtain timely information on ovulation or pregnancy and thus to instruct the participant to continue engaging in intercourse or to stop the intervention. We will determine whether the women have an ovulation response based on the serum progesterone level, and there will be three possible scenarios—ovulation, delayed ovulation, or no ovulation—as follows:
*Ovulation*: Serum progesterone level on day 21 of the cycle > 3 ng/ml. A serum pregnancy test will be performed 1 week later to exclude pregnancy. In the letrozole and placebo letrozole groups, letrozole or placebo letrozole will be started between days 3 and 7 of the new cycle, and the letrozole or placebo letrozole dose will be maintained at the same level as the previous cycle.*Delayed ovulation*: Serum progesterone level on day 21 of the cycle < 3 ng/ml. In this case, we will wait 1 week and then check the serum progesterone level again. If the second measurement shows that ovulation occurred (serum progesterone > 3 ng/ml), a serum pregnancy test will be performed 1 week later to exclude pregnancy. In the letrozole and placebo letrozole groups, letrozole or placebo letrozole will be started between days 3 and 7 of the new cycle, and the letrozole or placebo letrozole dose will be maintained.*No ovulation*: Negative serum progesterone on day 21 and day 28. In the letrozole and placebo letrozole groups, women will take letrozole or placebo letrozole on day 28 of the cycle, and then one more tablet per day will be given for 5 consecutive days until the maximum daily dose of three tablets per day. Day 28 will be defined as day 1 of the next cycle, and a serum progesterone measurement will be made every week until ovulation.

Every menstruation will be recorded, including the date, amount, and duration of menstruation.

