The analysis of secondary (supplemental) outcomes measured over time will entail the application of statistical methods that have been developed for correlated data because repeated observations will be made over time for each individual. For secondary outcomes such as hormone levels, a linear mixed-effect model will be fit where the main independent variables will be treatment group, time, and their interaction as well as the designed randomization stratification factors as covariates. Logistic regression models will be used in secondary analyses to evaluate the predictive value of treatment arm, clinical site, body mass index, and other explanatory variables on binary outcomes (e.g., live birth, abortion). Cox proportional hazards models and the Kaplan-Meier method will be used to compare time to pregnancy in the treatment groups. Effects on QOL, as determined by the change from baseline physical and mental component scores, will be analyzed by univariate and multivariate ANCOVA. The adequacy of blinding will be tested by Fisher’s exact test comparing true group assignments with participant guesses, including “don’t know.” In order to evaluate acupuncture as a unique therapy, the combination of the personalized acupuncture group and fixed acupuncture group will also be compared with the combination of the letrozole and placebo letrozole groups for the analysis of primary outcome. Differences in AE rates will be analyzed in a negative binomial generalized linear model. A *P* value < 0.05 with a two-tailed test will be considered significant. All statistical analyses will be performed using IBM SPSS Statistics version 21.0 software (IBM Corp., Armonk, NY, USA).

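### AEs are recorded at every visit and visit frequency differs several-fold by arm, so the acupuncture-versus-pill AE comparison is confounded with how often women are asked

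*Protocol article*

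**What the plan says.** Under Study-specific visits and procedures, the article states that "Women will attend up to five different clinic visits", one type being the treatment visits, and that "Adverse events (AEs) and concomitant medications will be recorded at every visit". Table 3 in the same section marks AE assessment in the treatment-visit columns of all four arms. In the same block, for the two acupuncture arms only, it has a row that begins "Acupuncture treatment (three times weekly".

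The Intervention section gives acupuncture "three times per week with a maximum of 48 treatment sessions over 16 weeks".

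The cycle contacts apply to every arm and are set under Treatment visits: "A serum progesterone measurement will be taken in the local laboratory on day 21 of the menstruation cycle", then "If ovulation occurs, a serum pregnancy test will be performed 1 week later". Without ovulation, progesterone is checked weekly. The pill arms have no other treatment-phase contacts. The Blinding section puts pill treatment at four cycles.

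AEs are a secondary outcome. The Adverse events section reports the percentage of women with AEs and SAEs, and Data analysis adds that "Differences in AE rates will be analyzed in a negative binomial generalized linear model", at a two-sided 0.05 level.

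**The concern.** An AE that is collected by asking at visits can only be recorded if the woman still remembers it, or still has it, when she is next asked. A mild event lasting a day or two is likely to be caught when sessions are two or three days apart, and may be lost when contacts are one to three weeks apart. If contact frequency is set by the arm, the recorded rate mixes the true event rate with the chance of being asked.

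The bias has a fixed direction: it raises the recorded AE rate in the acupuncture arms relative to the pill arms. Acupuncture could appear to cause more minor AEs than letrozole or placebo when true rates are equal, or a true excess on letrozole could be masked. An offset for time at risk would not correct this, because the imbalance lies in the number of contacts and not in the length of follow-up. Nor can a later analysis recover pill-arm events that were never elicited.

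**Working it through.** **Contacts at which AEs are recorded, 16-week treatment phase**

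- Acupuncture sessions: 3 per week × 16 weeks = 48, which reproduces the stated maximum.
- Cycle contacts, any arm: day 21 and one contact a week later, 2 × 4 cycles = 8. If checks run weekly throughout, about 16.
- Ratio counting sessions only: 48/8 = 6 to 48/16 = 3.
- Ratio counting the acupuncture arms' own cycle contacts too: (48 + 8)/8 = 7 to (48 + 16)/16 = 4.

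**What that could do to the comparison**

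The article gives no recall period, AE frequency or dispersion, so these are assumptions. Suppose that true AE rates are equal, that contacts are evenly spaced over 112 days, and that the chance of an event being recorded halves every h days until the next contact. With k = ln 2 / h and a gap of L days, the average captured fraction is

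(1 − e^(−kL)) / (kL).

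The gap is 112/48 = 7/3 days for acupuncture, 112/8 = 14 days for 8 pill-arm contacts, and 112/16 = 7 days for 16.

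Example with h = 7:
- Acupuncture: kL = 0.231, captured fraction 0.89.
- Pills, 8 contacts: kL = 1.386, captured fraction 0.75/1.386 = 0.54.
- Apparent rate ratio: 1.65 from unrounded fractions.

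The false-positive rate comes from a Wald test on the log rate ratio, with 275 per arm, a true mean of 1 AE per woman and dispersion 1:

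SE² = (1/μ₁ + 1)/275 + (1/μ₂ + 1)/275, where μ₁ and μ₂ are the recorded means.

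For the example, SE ≈ 0.134 and ln(1.65)/0.134 ≈ 3.7, so the test rejects in about 96% of trials.

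| Recall half-life | Captured, acupuncture | Captured, pills (8 / 16 contacts) | Apparent rate ratio (8 / 16) | False-positive rate (8 / 16) |
|---|---|---|---|---|
| 7 days | 0.89 | 0.54 / 0.72 | 1.65 / 1.24 | 96% / 38% |
| 14 days | 0.94 | 0.72 / 0.85 | 1.31 / 1.12 | 56% / 15% |
| 28 days | 0.97 | 0.85 / 0.92 | 1.15 / 1.06 | 20% / 7% |
| 90 days | 0.99 | 0.95 / 0.97 | 1.05 / 1.02 | 7% / 5% |

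A harder recall rule, in which everything within 7 days is recorded and nothing after, gives a similarly wide spread. Two to three contacts in a 28- to 35-day cycle capture 14/35 = 40% to 21/28 = 75%, while weekly contacts capture 7/7 = 100% and leave no bias.

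With the same contact schedule in all arms, the expected ratio is 1.00 and the false-positive rate 5%.

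**The case against.** The strongest objection is that the article never says in so many words that each acupuncture session is an AE visit. The Treatment visits section describes only the progesterone and pregnancy tests, and the Intervention section speaks of sessions and appointments. In Table 3 the same mark is used for tests that are plainly not done 48 times, so it may only mean at some point in this phase. On that reading AEs follow the cycle schedule in all arms and the imbalance goes away. The reading is possible, but it is not stated. The text ties AEs to every visit, and Table 3 puts the sessions under the treatment visits. Sites that follow it as written would record AEs at sessions.

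A second objection is that elicitation wording and form fields are usually left to the full protocol or the case report form, which are not shown. That is fair for the detail. The point here, however, is a rule that the article does state, combined with arm-specific visit frequencies that it also states.

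Third, 48 is a ceiling: sessions can be missed, and treatment stops at pregnancy. Weekly contact is the stated rule for women who do not ovulate. Both narrow the gap, and both stand as limits on its size.

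Fourth, the consequence is bounded. The safety hypothesis in Objectives concerns miscarriage and pregnancy complications, for which follow-up is the same in all arms, including delivery records. SAEs are unlikely to be forgotten between visits. This also stands.

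**Conclusion.** The point holds on the plain reading: opportunities to record an AE differ about 3- to 7-fold by arm, and nothing in the article offsets this. The acupuncture-versus-pill contrasts, in the AE-rate model and in the percentage of women with AEs, are confounded with how often women are asked. The effect falls mainly on minor, short-lived events.

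A reader might infer that the AE comparison measures nothing but contact frequency, or that a large false excess for acupuncture is to be expected. The article supports neither. True differences also enter the comparison, and the size rests on recall. Across the assumptions tried, the apparent rate ratio runs from about 1.65 (8 pill contacts, 7-day half-life) to about 1.02 (16 contacts, 90 days), with false-positive rates from about 96% to 5%. Recall, mean AE count and dispersion are all assumed, so the bias could be serious or negligible.

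Nor does the problem reach every contrast. Personalized versus fixed acupuncture share a session schedule, and neither pill arm has sessions, so the session imbalance does not affect either within-type comparison. SAEs and outcomes from delivery records are little affected, and the primary outcome is not affected. The change should be made, because the comparison is a planned one and the remedy is cheap.

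**What to change.** In all four arms, ask about AEs since the last assessment with the same checklist at common time points that every arm already attends: day 21 of each cycle and the end-of-treatment visit. Day 21 is preferable to the later weekly checks because it is scheduled whether or not the woman ovulates, whereas the number of weekly checks depends on ovulation.

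Base the between-arm negative binomial model and the comparison of percentages on these elicited events plus all SAEs from any source. Keep recording AEs at acupuncture sessions, tag them by source, and report them descriptively.

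If acupuncture sessions are not meant to be AE visits, amend the statement under Study-specific visits and procedures and the AE row of Table 3 to say so.

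The cost is a source field on the AE form and a short addition to the protocol and analysis plan. No visits are added. The downside is that some minor session-reported AEs leave the comparative model, although they are still reported.

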**Fig. 2 Fig2:**
[figure not shown]
Study flowchart

**Table 3 Tab3:** Overview of the study visits

	Screening visit	Baseline visit	Treatment visits (16 weeks)				End-of-treatment visit	Pregnancy visit
			Personalized acupuncture	Fixed acupuncture	Letrozole	Placebo letrozole		
Sign consent	×							
History	×						×	
Urine pregnancy test	×	×	×	×	×	×		
Physical examination	×						×	
Transvaginal ultrasound	×							×
Semen analysis	×							
Tubal patency test	×							
HPV or TCT	×							
Preconception counseling	×							
Fasting blood for laboratory tests	×						×	
Blood sample collection		×					×	
Serum progesterone assay	×		×	×	×	×		×
Serum HCG assay	×	×	×	×	×	×		×
Questionnaires		×					×	
Acupuncture treatment (three times weekly)			×	×				
Assess adverse events and concomitant medications			×	×	×	×	×	×
Pregnancy and neonatal records								×

Physical examination: weight, height, waist circumference, hip circumference, Ferriman-Gallwey/acne

Fasting blood for laboratory test: follicle-stimulating hormone, luteinizing hormone, sex hormone–binding globulin, total testosterone, free testosterone, estradiol, prolactin, fasting blood glucose, fasting insulin, C-peptide, glycated hemoglobin, cholesterol, triglycerides, high-density lipoprotein cholesterol, low-density lipoprotein cholesterol, complete blood count, thyroid profile, renal profile, and liver profile

Transvaginal ultrasound: endometrial thickness, ovarian volume, antral follicle count, and size of ovarian cysts or developing follicles

Preconception counseling: TORCH (toxoplasmosis, rubella, cytomegalovirus, and herpesvirus) and human immunodeficiency virus screening

Blood sample collection: serum for the central core laboratory

*Abbreviations: HCG* Human chorionic gonadotropin, *HPV* Human papillomavirus, *TCT* ThinPrep cytologic test

### Screening visit

Women will be screened in the morning after an overnight 12-h fast. Detailed information about the study design will be given.

#### Physical examination

Complete physical examinations will be performed, including measurement of height, weight, hip, and waist and vital signs. Height and weight will be recorded to the nearest 1 cm and 0.1 kg, respectively. Waist and hip circumference will be recorded to the nearest 1 cm. Hirsutism will be assessment by FG score, and acne will be assessed by standard acne lesion counts.

#### Transvaginal ultrasound of ovaries

Ovary size in three dimensions, the size of the largest ovarian follicle/cyst, the size of every follicle with a mean diameter > 10 mm, and the total antral follicle count (small follicles with a mean diameter of 2–9 mm) of both ovaries will be obtained through transvaginal ultrasound.

#### Pregnancy test

A urine and serum pregnancy test will be performed to exclude pregnancy.

#### Laboratory tests

Blood samples will be collected for the following measurements: total T, sex hormone–binding globulin (SHBG), FSH, LH, progesterone (P), estradiol (E2), PRL, glucose and insulin concentrations, HbA1C, C-peptide, and lipid profile (cholesterol, triglycerides, high-density lipoprotein cholesterol [HDL-C], and low-density lipoprotein cholesterol [LDL-C]), liver profile (ALT, AST, and total bilirubin), renal profile (BUN and creatinine), thyroid profile (TSH, T3, and free T4), complete blood count, and human papillomavirus test or ThinPrep cytologic test. All of these parameters will be measured in the local laboratories at each study site. The free androgen index will be calculated using measurements of total T and SHBG as previously described [5].

#### Preconception counseling

TORCH screening (toxoplasma, rubella virus, cytomegalovirus, herpesvirus), human immunodeficiency virus screening, and folic acid prescription will be included.

#### Progestin withdrawal

Women without evidence of ovulation on baseline screening will be provided progestin to induce withdrawal bleeding, with instructions to begin medication once eligibility has been determined. All participants will sign the consent form after the comprehensive counseling.

### Baseline visit

The baseline visit will take place around days 1–7 of a spontaneous menstruation cycle or after a withdrawal bleeding if a woman fulfills the inclusion criteria and has signed the consent form. Fasting blood samples will be obtained from the patients and will be shipped to the core laboratory for analysis and stored for a minimum of 5 years and may be further used in future studies, which is stated in the informed consent form (Supplementary file 2). Moreover, a urine or serum pregnancy test will be performed at this visit.

#### Questionnaires

Women will complete the following questionnaires: the 36-item Short Form Health Survey (SF-36) of health-related quality of life (QOL), the Polycystic Ovary Syndrome Quality of Life Questionnaire (PCOS-QOL), the Chinese Quality of Life (ChQOL), the Pittsburgh Sleep Quality Index (PSQI), the Zung Self-Rating Anxiety Scale (SAS), and the Zung Self-Rating Depression Scale (SDS).

The symptoms of PCOS are mainly differentiated in TCM as a liver-kidney yin-type deficiency or a spleen-kidney yang-type deficiency. The TCM syndrome diagnosis will be made by the PI and acupuncturist in each participating site according to a standard questionnaire during the baseline visit and the end-of-treatment visit. If the diagnosis differs between the PI and acupuncturist, they will discuss this until reaching an agreement. Syndrome differentiation in TCM entails the comprehensive analysis of clinical information gained by the four main diagnostic TCM procedures: observation, listening, questioning, and pulse analysis. All baseline measures will be repeated in all subjects at the end-of-treatment visit.

